### Sample size calculation

The primary outcome is the time to recover following surgery. A difference of 7 days was considered a clinically significant difference based on time to recover following TAH (28.1 days, SD 9.5), VH (21.3 days, SD 8.5) and LAVH (19.7 days, SD 7.5 days) in a study published in the *BJOG* by Ottosen et al. [7]. Using the mean and SD of the above data, a type 1 error of 0.01 and a power of 80% with a loss to follow-up of 20% produces a sample size of 49 patients per arm (total of 147). The reason for a type 1 error of 0.01 (two-sided) was for a Bonferroni adjustment for multiplicity to keep the overall *p* value to less than 0.05 after pairwise comparisons.

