### Safety monitoring and premature termination of study

All surgeries will be done by consultants competent in the relevant type of hysterectomy, i.e., for an example all hysterectomies will be done by specialists who have operated on a minimum of 25 procedures. Any complication would be managed as per standard guidelines and necessary multidisciplinary input sought if required. All complications will be reviewed by an independent clinical review panel comprising three experienced gynaecologists. A list of all the possible complications will be made available at each site. It is the responsibility of the researchers and all other grades of staff to inform the clinical review committee of any complication through incident report forms, which are available in each setting. The clinical review panel will assess if the complications in the TLH or NDVH group exceed in amount or severity compared to the standard treatment (TAH group). If so, the disadvantaged arm of the study will be terminated.

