Major complications (bladder, ureteric, bowel) are relatively rare in hysterectomy for benign surgery and as such a very large sample size would be needed if it was selected as the primary outcome. This is not feasible in our context and this study is underpowered to detect these problems. However, it could be assumed that if these complications were to occur, it would in some way be reflected by the time to recover and QALYs as these measures will show the overall quality of life of the individual concerned. Assessment of menopausal symptoms post-hysterectomy would need serum FSH levels before and after surgery if it is to be assessed in a quantitative manner, but it is not available in the public sector in Sri Lanka. Post-hysterectomy vaginal vault prolapse is a rare long-term complication following hysterectomy which would require follow up at least of up to 10 years, which is not feasible in our setting.

Despite these disadvantages, this randomized controlled trial will provide level 1 evidence regarding the three main methods of hysterectomy in terms of operative time, postoperative hospital stay, cost, convalescence, sexual dysfunction, bladder, bowel function and QALY’s. It will also establish a quantifiable and reproducible method of accessing outcomes for benign gynaecological surgery.

Although exact figures for rates of hysterectomy are difficult to obtain for developing countries it can be assumed to be very high due to the non-availability of levonorgestrel intrauterine system and other medical alternatives due to financial constraints, and as such TAH is often offered by default. This study will shed light on whether it is indeed the most appropriate in terms of health- related quality of life and cost-effectiveness. If it is not, i.e. if NDVH or TLH is better than TAH, it will suggest a change in attitude of gynaecologists, resource allocation from the Ministry of Health and even postgraduate training to lay more emphasis on alternative methods of hysterectomy.

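### The arm-termination rule is triggered by any excess of complications over TAH and, as printed, makes no allowance for chance

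*Protocol article*

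**What the plan says.** The section on safety monitoring and premature termination states: "All complications will be reviewed by an independent clinical review panel", a group of three gynaecologists. Staff are to "inform the clinical review committee of any complication through incident report forms". The panel is then to "assess if the complications in the TLH or NDVH group exceed in amount or severity compared to the standard treatment (TAH group", and the next sentence gives the consequence: "If so, the disadvantaged arm of the study will be terminated".

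The Outcome measures section lists the complications. They run from bladder, ureteric and bowel injury to transfusion, fever and infections, and they include conversion to laparotomy. The section on patient selection and data collection mentions conversion only at TLH or NDVH. Table 1 provides scheduled complication sheets, filled in by a research assistant, for the operative, postoperative, 6-week and 6-month periods.

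The Sample size calculation uses "a type 1 error of 0.01 and a power of 80% with a loss to follow-up of 20" per cent, giving 49 per arm. The 0.01 is there to protect the pairwise comparisons. The Discussion says of the major visceral injuries that "this study is underpowered to detect these problems".

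**The concern.** Two arms with the same true risk will rarely show the same count. One of them will usually be higher, and at any single look a harmless arm is nearly as likely to be above TAH as below it. The printed rule turns that ordinary variation into a reason to terminate. It does so for two arms, on two criteria (amount or severity), and with conversion to laparotomy counted although it can arise only in TLH or NDVH. The efficacy comparisons have strict error control, while this comparison, which can end an arm, has none.

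At stake is the precision of the comparison with TAH for the closed route. Its recovery time, cost and cost-effectiveness would rest on the women operated on before closure. If the panel instead disregards a chance excess, as it sensibly might, it departs from the printed rule on a safety matter.

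**Working it through.** **Step 1. The plan's own figure.** Inputs from the Sample size calculation: difference 7 days, SD 9.5 (TAH) and 8.5 (VH), two-sided 0.01, power 80%, loss 20%.

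n = (2.576 + 0.842)² × (9.5² + 8.5²) / 7² = 38.7, so 39 per arm; 39 / 0.8 = 48.75, so 49. The stated figure reproduces and is not in dispute.

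**Step 2. Inputs for the termination rule.** The article gives no complication risk and no look times. Assumed:
- the same risk p per woman in all arms, 5% to 30%, with 1% as a low extreme;
- looks at 16 and 33 per arm, about one third and two thirds of 49. A look at 49 is left out because recruitment is then complete and there is nothing left to stop.

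The literal rule closes an arm if its count of women with a complication is higher than the TAH count at a look.

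**Step 3. One arm, one look.** With X and Y independent Binomial(n, p), P(X > Y) = (1 − P(X = Y)) / 2. For n = 16 and p = 10%, P(X = Y) = 0.241, so P(X > Y) = (1 − 0.241) / 2 = 0.38.

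**Step 4. Two looks, two arms.** For each possible pair of TAH counts (at 16 and at 33), let s be the probability that an arm is above TAH at neither look. Given the TAH counts the two arms are independent. So the chance of closing a given arm is the average of 1 − s over the TAH counts, and the chance of closing at least one is the average of 1 − s². The exact results are:

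| True risk, all arms | A given arm closed | At least one arm closed |
|---|---|---|
| 1% | 23% | 40% |
| 5% | 47% | 65% |
| 10% | 52% | 69% |
| 20% | 55% | 72% |
| 30% | 56% | 73% |

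If TAH has a 20% risk and both other routes truly halve it to 10%, at least one of them is still closed in 28% of trials. These figures count amount only. The severity criterion and conversion to laparotomy can only add closures.

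**Step 5. Effect on power.** An arm stopped at 16 women has 16 × 0.8 = 12.8, so about 12 evaluable. The common SD is √((9.5² + 8.5²) / 2) = 9.01.
- Against a full TAH arm of 39: SE = 9.01 × √(1/12 + 1/39) = 2.98 and 7 / 2.98 = 2.35. The t-test power at two-sided 0.01 is 38%, or 36% if the SD of 8.5 is kept for the small arm. The normal approximation gives 41%.
- Against concurrent TAH only (12 v 12): SE = 9.01 × √(2/12) = 3.68 and 7 / 3.68 = 1.90. The t-test power is 21%.
- For reference, 39 v 39 gives 78% by the t-test and 80% by the plan's normal formula.

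**Step 6. What an allowance for chance would do.** Illustration: a one-sided Fisher exact test against TAH at the same two looks, same exact method.

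| Level | At least one harmless arm flagged (risk 5% to 30%) | True 10% (TAH) v 30% flagged, per arm |
|---|---|---|
| 0.01 | under 0.1% to 1.4% | 29% |
| 0.05 | 1% to 7% | 57% |

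**The case against.** The strongest reply is that the panel is an "independent clinical review panel comprising three experienced gynaecologists" asked to assess, not a counting device. Clinicians would not close an arm on a difference of one fever, and a charter or full protocol may hold the operating rules. This stands in part. Missing look dates and minimum numbers are not faults in a journal article, and the mechanical comparison above is a literal reading, not a forecast. It does not remove the point, because the article states the trigger and makes termination follow from it, with no word that would let the panel set aside a chance excess.

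A reader might infer that the rule would close a harmless arm in most trials. The documents do not support that as a statement of fact. It needs literal application, assumed risks and assumed looks. For one named arm it is about even, and at 1% risk even the either-arm figure is below half.

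A reader might also infer that a closed route drops out of the primary objectives. It does not. The article retains data after surgery and analyses all randomised women, so that route is still estimated, less precisely.

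Two supporting arguments should not be pressed. The admission of low power concerns rare visceral injuries, while the termination rule covers all complications. Replacing incident forms with scheduled sheets would also not cure unblinded reporting, since only the statistician is blinded.

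Finally, caution towards the two comparison routes is a legitimate choice, and any evidence level delays action on a real excess. That stands, and it is why the level belongs to the panel.

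**Conclusion.** The concern holds for the rule as printed: it links any excess in amount or severity to termination and leaves no room for chance. Applied literally with equal true risks of 5% to 30% and looks at 16 and 33 per arm, it closes at least one of the two arms in about 65% to 73% of trials and a given arm in about 47% to 56%. At 1% risk the either-arm figure is about 40%. An arm closed at 16 women would keep roughly 35% to 40% power against a full TAH arm, or about 21% against concurrent controls only, where 80% was planned.

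The wording problem is certain. Confidence in the size is moderate, because the risks, the look times and the literal reading are assumptions. This should be fixed, but it is not a flaw that invalidates the design.

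**What to change.** Reword the safety section so that a numerical excess prompts panel review and does not by itself terminate an arm. Then state:
- a pre-set evidence level, chosen by the panel with the statistician, for the proportion of women with a complication compared with concurrent TAH;
- a few fixed enrolment counts before recruitment ends at which it is applied;
- that the counts come from the scheduled Table 1 sheets, for completeness, with incident forms kept for speed;
- how conversion to laparotomy is handled in the comparison, since TAH cannot contribute any;
- the resulting false-closure probability;
- that the panel's clinical judgement on serious events is unaffected.

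The cost is a short amendment, with no extra patients. The downside is slower action on a real excess. In the Fisher illustration, a true 10% versus 30% is flagged before recruitment ends in only about 29% (level 0.01) to 57% (level 0.05) of trials per arm. The panel should see that trade-off when it chooses the level.

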### Main ethical issues

All three hysterectomy methods described above are standard treatment modalities in operative gynaecology. Therefore, we believe that we are not intentionally harming patients by including them in this clinical trial.

### Dissemination policy

The results of the study will be submitted for publication to peer-reviewed medical journals and presented at symposia regardless of the outcomes.

## Discussion

Studies in low-resource settings are hampered by financial limitations and feasibility in terms of time and collection of good quality accurate data. This protocol considers many relevant aspects concerned with the comparison of total abdominal, non-descent vaginal and total laparoscopic hysterectomy in one study for a lower-middle-income country where evidence on surgical outcomes especially in the form of randomized controlled trials are hard to come by. We believe these reasons make this protocol appealing for other researchers in similar settings.

As this is a multicentre study the involvement of multiple surgeons is inevitable and this can raise the issue of various skill levels and affect the outcome of surgery rather than a single operator. Although the issue of multiple surgeons is a limitation to the study itself, the generalisability of the results to the rest of the country would be more in our design of a pragmatic multicentre study involving multiple surgeons for each method rather than a single-centre study with a single surgeon for each method. In a study of this nature, it would not be possible to blind the patients nor the surgeons as the scars are distinct in each method. Although this is a limitation it is unavoidable and only the statistician will be blinded. The use of objective questionnaires, for patients’ as well as for assessors will also help to minimize bias [12].

The primary outcome, of time to resume usual activities, could be subject to recall bias. As it is a patient-reported outcome it has the advantage of being the best estimator of convalescence in the eyes of patients despite being subjective. Pelvic organ function is also assessed through patient-filled questionnaires as there is no objective method of assessing postoperative pelvic organ function. Although patient-reported outcomes can be subjective, validated questionnaires such as the ones used in this study make these assessments more valid and reliable. These questionnaires are the only available, non-invasive and generically applicable tools that can be used in low-resource settings.

Major complications (bladder, ureteric, bowel) are relatively rare in hysterectomy for benign surgery and as such a very large sample size would be needed if it was selected as the primary outcome. This is not feasible in our context and this study is underpowered to detect these problems. However, it could be assumed that if these complications were to occur, it would in some way be reflected by the time to recover and QALYs as these measures will show the overall quality of life of the individual concerned. Assessment of menopausal symptoms post-hysterectomy would need serum FSH levels before and after surgery if it is to be assessed in a quantitative manner, but it is not available in the public sector in Sri Lanka. Post-hysterectomy vaginal vault prolapse is a rare long-term complication following hysterectomy which would require follow up at least of up to 10 years, which is not feasible in our setting.

Despite these disadvantages, this randomized controlled trial will provide level 1 evidence regarding the three main methods of hysterectomy in terms of operative time, postoperative hospital stay, cost, convalescence, sexual dysfunction, bladder, bowel function and QALY’s. It will also establish a quantifiable and reproducible method of accessing outcomes for benign gynaecological surgery.

Although exact figures for rates of hysterectomy are difficult to obtain for developing countries it can be assumed to be very high due to the non-availability of levonorgestrel intrauterine system and other medical alternatives due to financial constraints, and as such TAH is often offered by default. This study will shed light on whether it is indeed the most appropriate in terms of health- related quality of life and cost-effectiveness. If it is not, i.e. if NDVH or TLH is better than TAH, it will suggest a change in attitude of gynaecologists, resource allocation from the Ministry of Health and even postgraduate training to lay more emphasis on alternative methods of hysterectomy.

There is very limited information on costs related to healthcare interventions in Sri Lanka possibly due to a misconception of *‘free health’*. The societal viewpoint in calculating costs in our study will generate an accurate picture of both direct hospital-related and indirect patient-related costs. The micro-costing approach used in this study is reported to be the most accurate method in calculating hospital cost [25]. Therefore, this study will provide valuable information on costing a surgical intervention, the methodology of which will be helpful across the board for other specialities as well as similar scenarios in other developing countries.

Sri Lanka is a lower-middle-income country, and as such it is important for us to enquire in to cost to ensure that maximum value for money is obtained with the limited resources at hand. Therefore, cost-effectiveness should be the benchmark to assess healthcare interventions in such a backdrop. This study will shed light on the optimum type of hysterectomy in terms of cost-effectiveness considering both the clinicians and patients’ perspectives.

### Trial status

The first patient was randomised to the trial on 1 August 2016. The trial is currently ongoing in the two centres and according to current rates of recruitment we envision the trial to complete recruitment by September 2017 with the last participant follow-up expected in September 2018.

Protocol version number 03: 26 July 2016

## Abbreviations

EQ-5D-3L: EuroQoL group questionnaire on health-related quality of life
ICIQ-FLUTS: International Consultation on Incontinence modular Questionnaire on Female Lower Urinary Tract Symptoms
ICIQ-VS: International Consultation on Incontinence modular Questionnaire on Vaginal Symptoms
NDVH: Non-descent vaginal hysterectomy
POP-Q: Pelvic organ prolapse quantification
QALYs: Quality-adjusted life years
RCT: Randomized controlled trial
TAH: Total abdominal hysterectomy
TLH: Total laparoscopic hysterectomy
